**Outpatient Screening Visit:**

1. Informed consent will be reviewed with and obtained from participant (Preview of consent to be performed by telephone prior to screening visit. Participant will also receive a copy of the consent by email or mail prior to screening visit).
2. History and physical will be performed.
3. Screening blood work (CBC, CMP, PT/PTT, CRP & ESR), a urinalysis, and pulmonary function tests, chest x-ray, and electrocardiogram will be obtained. A serum pregnancy test will also be obtained, if applicable. Some of the blood collected will be tested with research lab assays to confirm the efficacy of the study drugs. A urine sample will also be obtained for research lab assays for this same purpose.
4. If the volunteer passes all screening tests, s/he will be enrolled into the following groups (in order): pioglitazone plus oral placebo, zileuton plus oral placebo, pioglitazone plus zileuton, or two oral placebos.

**Outpatient Drug Treatment:**

1. Each volunteer will take the following:
   1. Pioglitazone 45 mg or matching placebo by mouth once daily for 2 weeks prior to admission.
   2. Zileuton 600 mg or matching placebo by mouth with food qid for 5 days prior to admission.

**Day 1:**

1. The volunteer will be admitted to the CRU.
2. Two (2) intravenous catheters will be started, one in each arm. Both catheters will be saline locked or maintained as continuous i.v. with normal saline at a keep-vein-open drip rate (10-20cc/hr).
3. Blood will be drawn for baseline testing, including screening labs and specific research assays for this study. A portion of this blood will also be tested for the TLR4 polymorphism (exploratory endpoints). A small drop of blood will also be taken to check a blood glucose level. A urine sample will also be obtained for research lab assays.
4. A urine pregnancy test will also be obtained, if applicable, to confirm non-pregnancy prior to [18F]FDG administration.
5. FDG-PET/CT scan will be obtained followed immediately by a second CT scan*.* The volunteer will have been instructed to be NPO for at least 4 hours prior to the PET scan.
6. Twelve hours before the bronchoscopy is scheduled, the subject will receive one tablet of oral sulfamethoxazole-trimethoprim (80/400) or oral amoxicillin (500 mg.) by mouth.
7. The volunteer will be NPO after midnight in preparation for bronchoscopy the following morning.
8. Pioglitazone/placebo will be given once daily and zileuton/placebo will be given qid until the morning of Day 3.

**Day 2:**

1. The volunteer’s temperature will be checked twice during the hour before their bronchoscopy.
2. One hour prior to bronchoscopy, the volunteer will receive a second dose of one tablet of the oral antibiotic: sulfamethoxazole/trimethoprim (80/400) or amoxicillin (500 mg.).
3. The volunteer may receive pre-procedure medications (Demerol, Vistaril), before the bronchoscopy.
4. During the bronchoscopy, endotoxin 4 ng/kg will be instilled into a middle lobe segment of the right lung as described above. The volunteer’s vital signs and oxygen saturation will be monitored closely. Oxygen will be administered to maintain their saturation level per protocol.
5. Once the volunteer returns to his/her room at the CRU, s/he will be observed per protocol for the rest of the day. These observations include: checks of vital signs, oxygenation, and symptoms (q 30 min x 4 hr, q 1 hr x 4 hr, and then q 4 hr until completion).
6. After the bronchoscopy, the i.v. fluids will be maintained until the volunteer can tolerate oral medications and nutrition.
7. Acetaminophen will be administered as needed.
8. The volunteer will be NPO after midnight in preparation for the PET scan and BAL the next day.
9. I.v. fluids will be given beginning at midnight to maintain hydration while volunteer is NPO.

**Day 3:**

1. The subject will have blood drawn in the morning for repeat testing of CBC, CMP, CRP and ESR. Additional blood will again be drawn for research lab assays. Any values outside normal expected values (see exclusion criteria) will be reviewed by one of the investigators, and a decision will be made concerning whether continued observation in the hospital is required or out-patient follow-up is needed until resolution. A urine sample will again be obtained for the same research lab assays as above.
2. If the second i.v. placed on Day 1 is not still functioning, a second i.v. catheter will be placed in the subject’s arm for the PET study.
3. The last dose of pioglitazone/placebo and zileuton/placebo will be administered in the morning.
4. A small drop of blood will be taken to check a blood glucose level.
5. FDG-PET/CT and second CT scan will be obtained in exactly the same manner as was done on Day 1 of this study.
6. Pulmonary function tests will be obtained.
7. The volunteer will be escorted back to his/her room at the CRU and will begin preparation for the 2nd bronchoscopy, which is for the bronchoalveolar lavage.
8. The subject may receive “pre-op” medications (Demerol, Vistaril) before the bronchoscopy as well as medication during the bronchoscopy (Versed and fentanyl). This will be at the discretion of the study physician to reduce any discomfort during the bronchoscopy.
9. During the bronchoscopy, the subject’s vital signs and oxygen saturation will be monitored closely. Oxygen will be administered to maintain their saturation level per protocol.
10. After the bronchoscopy and bronchoalveolar lavage (BAL), the subject will be monitored closely for the next several hours. Intravenous fluids will be maintained until the patient can tolerate oral medications and nutrition. After 4 hours of monitoring, if he/she is clinically stable, the monitors will be removed and s/he will be allowed to eat. Once fully recovered from the medications, the study physician will determine if the volunteer meets the criteria to be discharged to go home or whether s/he should remain in the CRU for overnight observation.

During the study, the volunteer will have PFTs measured after endotoxin instillation but prior to the BAL. BAL will not be performed if the FEV1 has decreased >20% from the pre-endotoxin baseline value. The change in pulmonary function will be followed until resolved or stabilized.

All volunteers will be observed as an inpatient for a minimum of 24 hours after endotoxin instillation (including any volunteers who receive endotoxin but withdraw from the study for any reason). The study will be terminated for any volunteer who experiences a serious adverse event (defined below). A follow-up call will be made 24 hours and 7+2 days after discharge to assess for any health problems.

Volunteers may also be asked to return within 3 days after discharge to repeat lab values if a greater than 25% change in white blood cell count, hemoglobin, hematocrit, BUN, or creatinine from baseline and/or an absolute lower limit of 7.0 grams of hemoglobin without symptoms is observed during the course of the study.

- 1. **Criteria for discharge from the CRU**

Subjects must meet the following criteria to be eligible for discharge the day after endotoxin instillation:

- No respiratory symptoms (cough, difficulty breathing, chest pain, wheezing, or excessive secretions) or need for intervention or assistance with O2 therapy or bronchodilators.
- Oral temperature less than or equal to 38.0° C.
- Heart rate 60-100 beats per minute.
- Systolic blood pressure >80 mmHg, <20% increase from baseline, <20% decrease from baseline.
  - - Diastolic blood pressure <20% increase from baseline, <20% decrease from baseline.
  - Pulse oximetry reading SpO2>90% without the use of supplemental O2 therapy.
  - No intervention required for treatment of malaise, or myalgia.
  - FEV1 at least 81% of baseline.
  - Absence of any other symptom or set of symptoms which in the judgment of the investigator requires additional observation in the CRU or hospital.

Beyond the first day after endotoxin instillation, discharge decision will be based on the investigator’s best medical judgment using the following criteria: lack of progression of the abnormality necessitating continued observation, stabilization or clinical improvement of the abnormality, and whether there is need for ongoing treatment.

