# Table of Protocol-Required Procedures FOR VOLUNTEERS RECEIVING ENDOTOXIN

| **PROCEDURE** | **Screen** | **Outpatient Drug Treatment (2 weeks)** | **Day 1 (Inpatient)** | **Day 2**  **(Inpatient)** | **Day 3**  **(Inpatient)** | **Day 4** | **Day 4+2 d**** | **Day 10 + 2 d** |
| --- | --- | --- | --- | --- | --- | --- | --- | --- |
| Inclusion/Exclusion criteria | X |  |  |  |  |  |  |  |
| Informed consent | X |  |  |  |  |  |  |  |
| Height/weight/VS | X |  |  |  |  |  |  |  |
| History and physical exam | X |  |  |  |  |  |  |  |
| Chest X-ray | X |  |  |  |  |  |  |  |
| Electrocardiogram (ECG) | X |  |  |  |  |  |  |  |
| Pulmonary function test (PFT) | X |  |  |  | X |  |  |  |
| Blood work: CBC, CMP, CRP, ESR, PT/PTT* | X |  | X |  | X |  |  |  |
| Blood sample for research lab assays | X |  | X | X | X |  |  |  |
| Urine sample for research lab assays | X |  | X |  | X |  |  |  |
| Urinalysis | X |  |  |  |  |  |  |  |
| Serum hCG | X |  |  |  |  |  |  |  |
| Urine hCG |  |  | X |  |  |  |  |  |
| Pioglitazone+placebo, zileuton+placebo, pioglitazone+zileuton, or placebo+placebo |  | X | X | X | X |  |  |  |
| Medication diary |  | X |  |  |  |  |  |  |
| FDG-PET scan |  |  | X |  | X |  |  |  |
| Sulfa vs amoxicillin |  |  | X | X |  |  |  |  |
| Nothing by mouth after breakfast |  |  | X |  |  |  |  |  |
| Nothing by mouth after midnight |  |  | X | X |  |  |  |  |
| Bronchoscopy |  |  |  | X | X |  |  |  |
| Endotoxin instillation |  |  |  | X |  |  |  |  |
| Bronchoalveolar lavage (BAL) |  |  |  |  | X |  |  |  |
| Phone call |  | X |  |  |  | X |  | X |
| CBC, CMP only** |  |  |  |  |  |  | X** |  |

* Not repeated on Day 3.

**This procedure is required only if participant has greater than 25% change in white blood cell count, hemoglobin, hematocrit, BUN, or creatinine or a decrease to 7.0 grams or below for hemoglobin level.

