**Primary Endpoints**

- Change in *K*i, the influx constant that describes the rate of [18F]FDG uptake into the right middle lobe, between baseline and post-endotoxin scans.
- Absolute *K*i after endotoxin

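### The baseline and post-endotoxin scans carry different fasting and i.v. instructions, so the single-group interim rule on Ki can absorb a difference in scan preparation

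*Protocol*

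**What the plan says.** Section 2.2 names two primary endpoints. One is the change in right-middle-lobe Ki "between baseline and post-endotoxin scans", which uses the Day 1 and Day 3 scans. The other is "Absolute *K*i after endotoxin", which uses the Day 3 scan only.

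Preparation for the Day 1 scan appears in two places. The Table of Protocol-Required Procedures has a row "Nothing by mouth after breakfast", marked for Day 1 only. The Day 1 timeline in Section 4.7 adds: "The volunteer will have been instructed to be NPO for at least 4 hours prior to the PET scan". The Day 1 lines are either saline locked or run with normal saline at 10–20 cc/hr.

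Preparation for the Day 3 scan is set out under Day 2: "The volunteer will be NPO after midnight in preparation for the PET scan and BAL the next day", and "I.v. fluids will be given beginning at midnight to maintain hydration while volunteer is NPO". The timeline gives neither the type nor the rate of that fluid.

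The Day 3 timeline then states: "FDG-PET/CT and second CT scan will be obtained in exactly the same manner as was done on Day 1 of this study". A finger-stick type glucose check is listed before the scan on both days. No limit, adjustment or other use of the result is stated in the text at hand.

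**The concern.** Section 1.1 acknowledges that FDG is a glucose analogue and that the scan in essence measures glucose uptake. Time since food is therefore a condition of measurement. The protocol takes trouble over reproducibility elsewhere: Section 4.4 even provides for a photograph so that the volunteer can be positioned identically at the second scan. Metabolic state gets no such matching. A volunteer may have had breakfast on the day of the baseline scan and cannot have had it on the day of the post-endotoxin scan.

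The change in Ki can then hold two things at once: the response to endotoxin, and whatever a different preparation does to Ki. This matters most for the interim rule in Section 6.2. That rule compares post-endotoxin with baseline Ki inside the first (pioglitazone) group, with no placebo group beside it. Its result bears on whether the pioglitazone plus zileuton group is enrolled, and hypothesis 3 in Section 1.2 cannot be tested without that group.

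**Working it through.** **Inputs.** Interim threshold: a 30% drop from baseline (Section 6.2). Planning difference 50%, SD about 25%, residual SD 23%, power 0.8, alpha 0.05, 6 per group (Sections 3.4 and 6.1). Sidedness is not stated, so two-sided is assumed. The documents give no figure for the effect of fasting or fluid on Ki, so every shift below is an assumption shown over a range.

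**1. The plan's own figure.** A two-sample t test for a difference of 50 gives 5.09, so 6 per group, at SD 25, and 4.52, so 5 per group, at SD 23. Power at 6 per group is 0.876 (SD 25) or 0.923 (SD 23). The stated sample size is reproduced; it serves only as the base for step 5.

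**2. The instructions side by side.**

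| | Day 1 scan | Day 3 scan |
|---|---|---|
| Food | breakfast allowed, then at least 4 h without intake | nothing from midnight |
| I.v. fluid | saline lock, or normal saline at 10–20 cc/hr | hydration from midnight; type and rate not given |
| Glucose check | yes | yes |

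No clock time is given for either scan, so the difference in fasting hours cannot be calculated.

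**3. Between-group contrasts.** Let d1 and d0 be the true changes in two groups.
- Common additive shift c: (d1 + c) − (d0 + c) = d1 − d0, so the bias is 0.
- Common multiplicative shift m on the Day 3 scan, with equal mean baselines B and post-endotoxin values P1 and P0: (mP1 − B) − (mP0 − B) = m(P1 − P0). The contrast is rescaled, but it stays at 0 when the drug does nothing.

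**4. Interim rule.** There is no comparator, so nothing cancels. With true post/baseline ratio r, the observed ratio is m × r. At the threshold the observed ratio is 0.70, so r = 0.70/m.

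| Assumed shift | 0.70/m | True change behind an observed 30% drop | Observed change if the true change is nil |
|---|---|---|---|
| −20% (m = 0.8) | 0.875 | −12.5% | −20% |
| −10% (m = 0.9) | 0.778 | −22.2% | −10% |
| +10% (m = 1.1) | 0.636 | −36.4% | +10% |
| +20% (m = 1.2) | 0.583 | −41.7% | +20% |

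**5. Noise in the change endpoint.** If the shift varies between volunteers with SD s, the total SD is √(SD² + s²).

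| s (points) | Total SD from 25 | Power, n = 6 | Total SD from 23 | Power, n = 6 |
|---|---|---|---|---|
| 0 | 25.0 | 0.876 | 23.0 | 0.923 |
| 10 | 26.9 | 0.825 | 25.1 | 0.874 |
| 20 | 32.0 | 0.684 | 30.5 | 0.726 |
| 30 | 39.1 | 0.517 | 37.8 | 0.543 |

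The planning SD comes from the earlier lovastatin study. If that study prepared its scans in the same way, some of this noise is already in the 23–25%. The documents do not say.

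**The case against.** Several points on the other side stand.

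- The sameness sentence can fairly be read as covering acquisition (tracer dose, framing, CT settings, positioning). Four hours is a minimum, which a fast from midnight would normally also meet. The two instructions are therefore unmatched rather than strictly contradictory. The breakfast row still shows that different preparation was planned.
- All groups follow the same schedule and the hypotheses compare groups, so a common shift mostly cancels there. Absolute post-endotoxin Ki cannot carry a Day 1/Day 3 mismatch at all.
- Glucose is already checked before both scans, and Section 4.4 provides for a measured input function. How these enter the analysis may be set out elsewhere.
- Fasting from midnight before bronchoscopy is an aspiration precaution (Section 5.7), and the outpatient zileuton or placebo is taken with food (Section 4.2). The investigators are not free to choose any interval.

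A reader might infer two stronger things, and the documents support neither. The first is that the i.v. fluids differ metabolically. Day 1 itself allows running saline, and nothing says the Day 3 fluid contains glucose. The second is that pioglitazone, as a diabetes drug, makes the shift unequal between groups and so biases the drug comparison. The volunteers are healthy and pioglitazone is being taken at both scans. No data are given on how it alters the response of lung Ki to fasting. An unequal shift is neither shown nor excluded.

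**Conclusion.** The concern holds in a limited form. Scan preparation differs between the two days, so the within-volunteer change in Ki can include a difference in metabolic state. The consequence is small for the between-group tests: no bias from a common additive shift, and possibly some loss of precision. It is largest for the interim rule, where the shift enters undiluted. Under an assumed ±10% multiplicative shift, an observed 30% drop means a true change of −22% or −36%; under ±20%, −12.5% or −41.7%. These figures show how sensitive the rule is and do not estimate the actual effect. Neither the size nor the direction of a preparation effect can be derived from the documents. This is a worthwhile, low-cost improvement and not a flaw that undermines the primary comparison.

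**What to change.** Reconcile the breakfast row in the procedures table with the Day 1, Day 2 and Day 3 entries in Section 4.7, so that both scans follow one common fasting and i.v. fluid specification. The investigators should choose that specification within their bronchoscopy and dosing constraints; this review does not say which of the present instructions is right. State in the Day 3 entry whether the sameness sentence covers preparation as well as acquisition. Record hours since last food at each scan, next to the glucose checks already planned, so that any remaining difference can be examined before the interim decision is made.

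The cost is a wording change and one extra recorded item, with a longer fast or a moved scan time on one of the two days.

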**Post-treatment period (defined as time of discharge from CRU until 10 days post-discharge).**

The volunteer will be given contact numbers for any problems encountered during this follow-up period. The research staff will contact the volunteer the next day (Day 4 for volunteers receiving endotoxin and Day 2 for volunteers undergoing BAL alone) and 7-9 days post discharge concerning any health-related problems.

1. **ADVERSE EVENT REPORTING AND DATA/SAFETY MONITORING**
   1. **Definitions**

The following definitions of adverse event and serious adverse event will be used for this study.

**Adverse event (AE):** AEs are defined conventionally, as any untoward medical occurrence during the planned observation period in a research participant that develops following test drug administration. The AE and drug administration do not have to be causally related.

**Serious adverse event (SAE):** SAEs are also defined conventionally as any medical occurrence that results in death, is life-threatening, requires inpatient hospitalization, results in persistent or significant disability, is a congenital anomaly or birth defect, or is an event requiring medical intervention to prevent any of these examples of an SAE.

SAEs may be mild (transient, easily tolerated by the participant), moderate (causes discomfort or interrupts the study or the participant’s usual activities), or severe (causes considerable interference with usual activities) in severity. Any criterion outside of the above boundaries must be documented as present for >2-4 hours, in order to be considered ‘more severe’.

- 1. **Causality of adverse events**

The causality of each AE in terms of relationship to administration of test drug will be assessed as definite (reasonable temporal relationship, with or without supporting laboratory data), probable (reasonable temporal relationship and other possible causes can be reasonably excluded), possible (reasonable temporal relationship and other possible causes are at least as or more likely), and unrelated (temporal relationship is not reasonable or other causes are reasonably more likely).

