## Safety Monitoring

We have not had any serious adverse events in the two clinical trials we have conducted, nor have any been reported in additional publications using this model[38-40](#_ENREF_38) since the original report was published[35](#_ENREF_35). Vital sign monitoring, inpatient observation, and outpatient follow-up (calls at 1 day and at 7+2 days after discharge) will be performed as we have published previously. The study will be terminated for any volunteer who experiences a SAE as defined above.

An independent, internal DSMB will monitor this trial. The DSMB will include senior investigators with expertise in critical care and infectious diseases. The DSMB will make recommendations to ensure data integrity and the safety of the volunteers.

DSMB Activities:

1) Review the research protocol and approve plans for data and safety monitoring.

2) Evaluate the progress of the study, including periodic assessments of data quality and timeliness, participant recruitment, accrual and retention, participant risk versus benefit, and other factors that can affect study outcome. Monitoring will also consider factors external to the study when interpreting the data, such as scientific or therapeutic developments that may have an impact on the safety of the participants or the ethics of the study. The principal investigator will make available to the DSMB any newly published information related to the use of endotoxin, pioglitazone, or zileuton which may affect patient safety.

3) Make recommendations to Washington University School of Medicine, the IRB, and investigators concerning continuation or conclusion of the trial.

4) Submit an annual report to the IRB.

5) Protect the confidentiality of the trial data and the results of monitoring.

6) Review data and safety issues (including any and all adverse events) and determine, with information provided by the study staff, whether the events should be regarded as study-related or unrelated. The DSMB will be empowered to stop the study, at their discretion, for safety reasons.

DSMB meeting frequency: The DSMB will meet to review the above listed information after the first two patients. They will then decide whether the study can go forward as planned, whether modifications are to be made in any procedures, and when to review the next set of data (but not less than every 8 patients).

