Stopping rules: The study will be stopped *for any individual subject* in the case of any SAE, defined prospectively. New recruitment/enrollment will be discontinued after any SAE until satisfactorily reviewed by the DSMB. The DSMB will make recommendations, if any, for changes to recruitment practices, the informed consent document, or safety/monitoring practices. All such recommendations will be communicated to the IRB, RDRC, and CRU.

The FDA will be notified of any study stoppages. Recruitment for study participation will resume *only* when we have received clearance from the FDA to do so. The entire study will be discontinued completely in the event of any study-related life-threatening event or death.

- 1. **Collecting/reporting of adverse events**

In the study in normal volunteers, all adverse experiences, whether expected or unexpected, will be recorded in the case report form (see Appendix III for samples) and reported to the DSMB for this study. Any adverse experience that occurs to a greater severity than expected will be reported to the IRB, RDRC, CRU, and FDA.

The IRB (Washington University School of Medicine Human Research Protection Office), RDRC, and CRU will be notified of any SAE within 10 working days of occurrence. The FDA will be sent an IND Safety Report within 10 working days of occurrence of any SAE. If the event is fatal or life threatening, the DSMB, IRB, and RDRC will be notified of the event within twenty-four hours. The CRU and FDA will be notified by telephone no later than 3 days after occurrence.

The IRB, RDRC, CRU, and FDA will receive annual reports regarding all adverse experiences.

- 1. **Follow-up of serious adverse events**

All SAEs will be followed up until resolution or permanent outcome of the event. All follow-up information will be included in the case report form.

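### The adverse-event causality grades in Protocol section 5.2 are neither ordered nor mutually exclusive: definite has a weaker test than probable, and possible overlaps unrelated

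*Protocol*

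**What the plan says.** Section 5.2 (Causality of adverse events) sets the object of the scale: "The causality of each AE in terms of relationship to administration of test drug will be assessed as definite", followed by three further grades. The four definitions are:

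- The top grade is worded "definite (reasonable temporal relationship, with or without supporting laboratory data", and it stops there without mentioning any rival explanation.
- The next grade down is worded "probable (reasonable temporal relationship and other possible causes can be reasonably excluded", so it adds a second requirement to the one on timing.
- The third grade is worded "possible (reasonable temporal relationship and other possible causes are at least as or more likely", which keeps the timing requirement and sets no ceiling on the rival explanation.
- The bottom grade is worded "unrelated (temporal relationship is not reasonable or other causes are reasonably more likely", so either limb alone is enough to meet it.

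The protocol gives no rule for choosing when two grades both apply, and no other criteria for relatedness.

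Section 5.3 (Safety Monitoring) uses relatedness in a different form. With information from study staff, the DSMB determines "whether the events should be regarded as study-related or unrelated". The stopping rules then say: "The entire study will be discontinued completely in the event of any study-related life-threatening event or death". The pause in enrollment does not depend on cause: "New recruitment/enrollment will be discontinued after any SAE until satisfactorily reviewed by the DSMB".

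**The concern.** A causality scale should run from strict to loose, and each event should have one place on it. Here the strongest label carries the lightest test: *definite* asks for timing only and makes laboratory support optional, while *probable* asks for timing and the exclusion of other causes. At the other end, *possible* has no upper limit on how likely the other cause may be, so it runs into *unrelated*.

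This touches ordinary events in this trial. Section 4.7 continues both study drugs until the morning of Day 3, so endotoxin, the first bronchoscopy and its sedation fall during dosing, and the second bronchoscopy with lavage falls on the last dosing day. Section 5.6 expects cough after bronchoscopy, fever after lavage in 10%-30%, and respiratory symptoms, mild fever, headache and muscle aches after endotoxin. It also lists headache and myalgia for pioglitazone, and headache and nausea for zileuton. Reasonable timing with a competing cause will therefore be a frequent situation, and it is where the definitions conflict.

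What is at stake is whether test-drug causality can be graded consistently. Section 5.7 gives monitoring of serious adverse events possibly linked to each drug treatment as the reason for sequential enrollment, so attribution to drug is part of the purpose of the design.

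**Working it through.** No sample size, power or event count enters, and the plan gives no figure to reproduce. The check applies the four definitions literally to every combination of two inputs taken from section 5.2:

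- timing: reasonable or not;
- other causes: excluded; less likely but not excluded; equally likely; more likely.

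Rules as written:

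- *definite* = timing reasonable;
- *probable* = timing reasonable AND other causes excluded;
- *possible* = timing reasonable AND other causes equally or more likely;
- *unrelated* = timing not reasonable OR other causes more likely.

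| Timing | Other causes | Grades met | Grades met if *definite* is set aside |
|---|---|---|---|
| reasonable | excluded | definite, probable | probable |
| reasonable | less likely, not excluded | definite | none |
| reasonable | equally likely | definite, possible | possible |
| reasonable | more likely | definite, possible, unrelated | possible, unrelated |
| not reasonable | any of the four | unrelated | unrelated |

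Three results follow.

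1. *Inversion.* Every row that meets *probable* or *possible* also meets *definite*. The top grade is the least demanding of the three related grades.
2. *Overlap.* With reasonable timing, the four rows meet 2, 1, 2 and 3 grades, so three of the four are ambiguous. The last spans the top and bottom of the scale. *Possible* and *unrelated* do not coincide: equally likely causes fit only *possible* of the two, and unreasonable timing fits only *unrelated*. They overlap in one row. Reading the qualifier in *unrelated* as a higher threshold shrinks that overlap but does not remove it, because *possible* has no ceiling.
3. *Gap.* A reader who treats *definite* as a slip and ignores it finds counts of 1, 0, 1 and 2 in the same rows: one situation has no grade and one has two. Repairing *definite* alone is not enough.

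The relatedness terms, side by side:

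| | Section 5.2 | Section 5.3 |
|---|---|---|
| Related to what | test drug | the study |
| Levels | four | two |
| Assigned by | not stated | DSMB, with information from study staff |
| Stated consequence | none | whole study ends if a life-threatening event or death is study-related |

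No text links the two columns.

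**The case against.** The strongest case on the other side is that little depends on the grade. A volunteer's participation stops for any serious adverse event. Enrollment pauses after any such event until the DSMB has reviewed it. The IRB, RDRC, CRU and FDA are told of any such event (section 5.4). All adverse experiences go to the DSMB, which may stop the study at its discretion for safety. None of this uses the section 5.2 grade, and section 6 plans no safety analysis by causality. All of that stands, and it limits the consequence.

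A reader might infer more than the documents support in three ways:

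- *That the ambiguous grade triggers study termination.* The termination rule rests on the DSMB's own call of study-related, which is a different question. An event caused by endotoxin or bronchoscopy could be study-related and unrelated to test drug. Section 5.2 is the only relatedness definition in the protocol, so influence on that call is conceivable, but the text does not make the grade an input.
- *That per-drug attribution tables will be distorted.* None is planned in the protocol.
- *That graders who know the treatment will choose the grade to suit.* Only volunteers are described as blinded and the group order is fixed, so staff awareness is plausible. But section 5.2 does not say who assigns the grade.

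It may also be said that experienced investigators would apply the conventional meaning of the labels. That is a hope about conduct. The written definitions say something else, and they apply to every adverse event.

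**Conclusion.** The point holds as a defect in the stated definitions. Section 5.2 inverts *definite* and *probable* and lets *possible* and *unrelated* overlap where timing is reasonable and another cause is more likely. With *definite* set aside, it has no grade for an event whose other causes are less likely but not excluded. Test-drug causality therefore cannot be graded consistently for the many events that coincide with endotoxin, bronchoscopy and sedation.

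The size is moderate. Individual stops, the enrollment pause and reporting of serious events are unaffected, and the link to whole-study termination is unstated. The conclusion rests on reading the definitions literally and on the four states of other causes covering all cases. It needs no assumption about event rates beyond the protocol's own account of expected effects. It is not something to leave to an analysis plan: the definitions are in the protocol and are wrong as written.

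**What to change.** 1. Reword the four grades so that they are ordered, mutually exclusive and exhaustive, with *definite* the strictest. Put a single boundary between *possible* and *unrelated*, so that an other cause that is somewhat more likely falls on one side and not between them. One layout that passes the table above, as an illustration: *definite* = timing reasonable, other causes excluded and supporting evidence present; *probable* = timing reasonable and other causes less likely or excluded, short of definite; *possible* = timing reasonable and other causes equally likely; *unrelated* = timing not reasonable, or another cause more likely. Where the last boundary lies is the sponsor's choice, provided it is one line.
2. Record relation to test drug separately from relation to endotoxin or procedure, if the case report form does not already do so. The sample forms are in an appendix that is not available here.
3. Reconcile section 5.2 with section 5.3 by stating how, if at all, the four grades map to the DSMB's call of study-related. This asks for a definition only and leaves the stopping rule as it is.

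Cost: protocol and case report form wording, and at most one extra field per event.
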